## Abstract

**Introduction:**

Adolescent girls and young women (AGYW) aged 15–24 years and adolescent boys and young men (ABYM) aged 15–34 years represent one of the populations at highest risk for HIV-infection in South Africa. The National Department of Health adopted the universal test and treat (UTT) strategy in 2016, resulting in increases in same-day antiretroviral therapy initiations and linkage to care. Monitoring progress towards attainment of South Africa’s 95-95-95 targets amongst AGYW and ABYM relies on high quality data to identify and address gaps in linkage to care. The aim of this study is to describe the current approaches for engaging AGYW and ABYM in the treatment continuum to generate knowledge that can guide efforts to improve linkage to, and retention in, HIV care among these populations in KwaZulu-Natal, South Africa.

**Methods and analysis:**

This is a mixed methods study, which will be conducted in uMgungundlovu district of KwaZulu-Natal, over a 24-month period, in 22 purposively selected HIV testing and treatment service delivery points (SDPs). For the quantitative component, a sample of 1100 AGYW aged 15–24 years and ABYM aged 15–35 years old will be recruited into the study, in addition to 231 healthcare providers (HCPs) involved in the implementation of the UTT program. The qualitative component will include 30 participating patients who were successfully linked to care, 30 who were not, and 30 who have never tested for HIV. Key informant interviews will also be conducted with 24 HCPs. Logistic regression will be used to model the primary outcomes on SDP types, while a time to event analysis will be conducted using a Cox regression model and adjusting the standard errors of the hazard ratio for the clustering of participants within SDPs. For qualitative data, a general inductive approach of analysis will be used.

**Dissemination:**

Findings from the study will be communicated to the study population and results will be presented to stakeholders and at appropriate local and international conferences. Outputs will also include a policy brief, peer reviewed journal articles and research capacity building through research degrees.

## Introduction

South Africa has the biggest HIV epidemic globally, with more than 7.8 million people living with HIV (PLHIV) in 2020 [1, 2]. Adolescent girls and young women (AGYW) aged 15–24 years represent one of the populations at highest risk for HIV-infection with an estimated HIV incidence of 1.5% [3]. Recent estimates show that 5.8% of adolescent girls aged 15–19 years were HIV-positive, compared with 4.7% of adolescent boys in that age group in 2017. In the 20–24 year age group, 10.9% of young women were HIV-positive compared with 4.8% of young men, while in the 25–29 and 30–34 year age groups, 27.5% and 34.7% of women were HIV-positive compared to 12.4% and 18.4% of men, respectively [3]. These figures highlight the specific vulnerability of AGYW, but they also show that adolescent boys and young men (ABYM) have a substantial risk of HIV.

Despite South Africa’s remarkable progress with antiretroviral therapy (ART) scale-up, ART coverage remains sub-optimal, particularly among HIV-positive AGYW and ABYM aged 15–24 years of whom only 55% of ABYM and 52% of AGYW were receiving ART in 2022 [4, 5]. Among people living with HIV aged 25–49 years, an estimated 63.1% were receiving ART, showing that there is a gap in linkage to, and retention in, HIV treatment services. Less than 70% of HIV-positive adolescents and young people aged 15–24 years were virally suppressed in 2022 [5]. These data highlight the challenges in linking and retaining adolescents and young people in HIV care, which is a major public health challenge for the South African National Department of Health.

Several factors account for the increased vulnerability of AGYW to HIV infection including intergenerational sexual relationships, gender power imbalances, gender-based violence, poverty and the low status of women, exclusion from economic opportunities and limited access to secondary schooling [6, 7]. Relationships with older men lead to power imbalances increasing the likelihood of intimate partner violence and the non-use of condoms during sex [7]. Socially excluded, marginalised adolescents and young people are particularly vulnerable to HIV infection and have poor access to HIV treatment and care, including people with disabilities, people who use drugs (PWUD), lesbian, gay, bisexual, transgender, and intersex (LGBTI) people, sex workers and undocumented migrants.

While AGYW are disproportionately affected by HIV, heterosexual men remain a critical population in HIV prevention. Men are less likely than women to test for HIV, engage in care in a timely way and remain in care [8–10]. In South Africa in 2018, 93% of women living with HIV were aware of their status compared to 88% of HIV-positive men [11]. Programs for the prevention of mother to child transmission of HIV enable women to access HIV testing services during routine antenatal appointments [10–12], which partly accounts for more women testing for HIV compared to men. Men report worrying that queuing outside a testing facility will be taken as evidence that they are living with HIV and avoid testing because they are terrified of a positive result [13]. While women have the benefit of a woman-centric health system, hegemonic masculinities largely exclude men from engaging with the health care systems [10]. HIV stigma, homophobia and gender norms also threaten men’s engagement in HIV prevention and treatment services [10].

As per the Joint United Nations Program on HIV and AIDS (UNAIDS) and the World Health Organisation (WHO) HIV strategic recommendations for countries, South Africa embarked on rolling out Universal Test and Treat (UTT) in September 2016. UTT is a WHO-supported initiative believed to be key for attaining the UNAIDS fast-track targets, aimed at reducing both HIV mortality and new infections to below 500 000 by 2020 [14]. The 2030 targets included the 95-95-95 targets, that state that 95% of PLHIV should know their status, 95% of those who know their status should be on treatment and 95% of those on treatment should be virally supressed [15]. UTT advocates that all individuals testing for HIV be initiated on treatment regardless of their clinical staging or CD4 count [16]. Through UTT, HIV transmission can be reduced by early initiation to ART coupled with adherence to treatment. This suppresses the viral load in infected persons, thus reducing the risk of transmission [17, 18]. To attain the potential benefits of UTT strategies, those who test HIV-positive must be linked to care for treatment initiation immediately after testing, regardless of where they tested [19]. Further, in order to achieve viral load suppression, all those on ART must be retained in care and adhere to lifelong ART [20].

Monitoring progress towards attainment of South Africa’s 95-95-95 strategic HIV treatment targets relies on high quality data to identify and address gaps in ART coverage, quality of care, prescription adherence and resource allocation. This study, which will monitor linkage to, and retention in HIV care among AGYW and ABYM in the uMgungundlovu district, KwaZulu-Natal, seeks to answer three questions. Firstly, what are the available service delivery models that are seeing higher linkage to care, and continuity of care and treatment among AGYW and ABYM? Secondly, what is the rate of acceptability and uptake of linkage to care by service delivery models–facility-only, community-only, and community-facility hybrid models? Thirdly, what factors influence acceptability and decision-making around the use of different service delivery models? The study aims to describe the current approaches used to engage AGYW and ABYM in the treatment continuum to generate knowledge which can be used to provide recommendations on the best practices for linkage to and retention in HIV care services for AGYW age 15–24 years and ABYM aged 15–35 years.

## Materials and methods

### The objectives of the study are

To describe the socio-demographic characteristics of AGYW (15–24 years) and ABYM (15–35 years) newly diagnosed with HIV who access HIV testing services in the uMgungundlovu district of KwaZulu-Natal, and to compare service delivery models.To describe the HIV testing experiences of AGYW and ABYM newly diagnosed with HIV in the uMgungundlovu district, comparing experiences across service delivery models.Among HIV-positive AGYW and ABYM, to quantify linkage to and retention in HIV care across different service delivery models, and to describe the factors associated with linkage to and retention in HIV care and health impacts thereof, in the uMgungundlovu district.To identify the mechanisms (reasoning and decision-making) and context (individual, structural social and health systems factors) that influence AGYW’s and ABYM’s uptake of HIV treatment and care services to describe the relative success of different HIV treatment service delivery models.

### Setting

The setting for this study, which will be conducted in the uMgungundlovu district in KwaZulu-Natal, have been described extensively in a complimentary study [21]. This predominantly rural district, with high HIV prevalence of 24% and 37% for people aged between 15–49 years among males and females, respectively [22], an 89% medically uninsured population, offers an excellent setting for monitoring UTT alongside interventions seeking to improve linkage to HIV care in the public sector. uMgungundlovu district is comprised of seven municipalities, all of which have rural areas, namely uMshwathi, Umgeni, Mpofana, Impendle, Msunduzi, uMkhambathini and Richmond.

### Study design

The SHeS’Cap-Linkage study, which compliments the SHeS’Cap-PrEP study [21], is a sequential, explanatory, mixed methods study that will be conducted at 22 purposively selected HIV testing and treatment service delivery points (SDPs). Unlike the SHeS’Cap-PrEP study [21] that focused on AGYW and ABYM who tested HIV negative at the selected pre-exposure Prophylaxis (PrEP) SDPs (health clinics, school-based and community-based centers), this study will focus on AGYW and ABYM with a positive HIV test outcome. These will include quantitative analysis of routine program monitoring data; monitoring of linkage to and retention in HIV care among AGYW and ABYM who test HIV-positive in selected SDPs, and in-depth interviews (IDIs) with AGYW and ABYM to describe the barriers to, and enablers of linkage to, and retention in HIV care. We will also conduct key informant interviews (KIIs) with healthcare providers involved in the implementation of the UTT program in the district.

The primary outcomes for this study are linkage to care within 14 days and retention in care at six months after HIV diagnosis. Linkage to care is defined as “the proportion of AGYW (15–24 years) and ABYM (15–35 years) per SDP per month who have been initiated onto ART as evidence by a record in their TIER.Net or for whom baseline CD4 results have been captured into their TIER.Net record within 0–14 days (within 2 weeks) of their HIV-positive test at enrolment.” Retention in care is defined as “the proportion of AGYW (15–24 years) and ABYM (15–35 years) per SDP per month for whom an entry has been captured into the National Health Laboratory Service (NHLS) for confirmed linkage at 6 months after their positive HIV test at enrolment.”

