### Sampling

#### Service delivery points (SDPs) and sample size for individuals to be enrolled

The criteria for selecting the 22 SDPs included in this study have been reported elsewhere [21], and the HIV testing number in these SDPs are >4000 clients per month. Published studies and previous surveillance data from KwaZulu-Natal province in South Africa demonstrate an average linkage to care rate of 62% post HIV testing. However, recent findings from a district neighboring uMgungundlovu, reported a linkage to care rate of 83% [23]. We assume the linkage to care rates in uMgungundlovu district municipality to be 10% higher than 62% reported from the province based on the possible impact of UTT on HIV uptake. Also, we intend to compare the three service delivery models (facility-based, school-based, and community-based) across the seven sub-districts in uMgungundlovu. Since the study is non-randomised (unmatched study) with purposive sampling, it will be exploratory in nature and will inform the rates of linkage to care based on the different SDPs to facilitate better planning for intervention studies.

Sample size calculations (Table 2) are illustrative of the power of the study design to detect difference in coverage by service delivery models and are based on the comparison of proportions between clusters of fixed sizes in each service delivery group at a specific time point (i.e., 6 months follow-up). The sample size was done for the comparison of mainly community versus facility service delivery models for all the participants with the assumption that the participants attending schools i.e., TVET colleges and High schools will be included in the facility and community-based arms. The number of clusters (SDPs) needed to detect a coverage difference between the community- and facility-based service delivery models with >80% power is 22 in total, translating to 11 in each model with 50 participants per cluster assuming an intraclass correlation coefficient (ICC) of 0.01 and significance level of 0.05 [24]. The sample and power calculation were done using Stata v14.2 [25]. The study will retain at least 80% power for a 20% dropout at 6 months of follow-up (m = 40 per cluster) and the design effect of 1.5 were deemed realistic for the study populations.

**Table 2 pone.0271942.t002:** Power and sample size for the comparison of service delivery model for the SHeS’Cap-Linkage study in uMgungundlovu district, KwaZulu-Natal, South Africa, 2021–2023.

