**Fig 1 pone.0271942.g001:**
[figure not shown]
An illustration of the study activities for the SHeS’Cap-Linkage study in uMgungundlovu district, KwaZulu-Natal, 2022.

Secondary data sources, including routine data from facility-based health information systems, routine data from district-level TIER.Net, data from the National Health Laboratory Service (NHLS) and data from the South African Medical Research Council (SAMRC)’s Rapid Mortality Surveillance (RMS) containing monthly information about deaths registered by the South African Department of Home Affairs will be used to obtain information on linkage to and retention in care in the SDPs where this project will be implemented. The RMS, therefore, will be used to confirm that the individual considered as not linked to care or not retained in care was not deceased. Table 4 gives an overview of the outcome variables, and data sources and tools.

**Table 4 pone.0271942.t004:** Roles of outcome variables in the SHeS’Cap-Linkage study in uMgungundlovu district, KwaZulu-Natal, 2021–2023.

Outcome variables	Examples of variables	Data sources and tools
• Proportion of AGYW and ABYM who have initiated ART as evidenced by a record in their TIER.Net within 14 days or for whom baseline CD4 results have been entered into their TIER.Net record within 1 month of their HIV-positive test result at enrollment. (Primary outcome)	• Patient receipt of HIV test result.	• Routine data (Clinical charts, clinic HIV testing and tracking registers, patient folders and TIER.Net*) and questionnaire data as necessary.
	• Patient attendance at first clinic appointment after receipt of HIV result.	
	• Enrolled patients taking up same-day initiation onto ART at diagnosis	
	• Proportion for whom ART initiation is within 2 weeks of a CD4 test	
	• ART initiation date recorded in clinical stationery and/or TIER.Net	
• Proportion of AGYW and ABYM for whom an entry has been captured into their TIER.Net record at 6 months after their positive HIV test at enrollment. (Primary outcome)	• Patient attendance at clinic as per contemporary NDoH guidelines at 6 months after HIV diagnosis	• Routine data (Clinical charts, clinic HIV testing and tracking registers, patient folders and TIER.Net*)
	• NHLS records of samples received at NHLS laboratory, as per contemporary NDoH guidelines (e.g., repeat CD4 or Viral Load results every 6 months)	• NHLS records
		• RMS
		• Baseline and follow-up questionnaires

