	• TIER.Net records at facility of NHLS results recorded within 1 month of the date each sample was sent	
	• Viral load suppression at 6 months	
• Proportion of enrolled participants testing HIV-positive and not yet initiating ART who are not retained in HIV care at 6 months after HIV diagnosis at initiation		• Routine data (Clinical charts, clinic HIV testing and tracking registers, patient folders and TIER.Net*)
• Further description of participants’ health seeking behaviour	• Participant experiences of seeking HIV testing and care prior to date of HIV diagnosis at enrolment in this cohort.	• In-depth interviews (IDIs)
	• Proportion of patients who are not retained in care after initiating ART	
• Clinic processes and data quality to support linkage to and retention in care.	• Completeness and location of post-test initiation (clinic/community/schools)	• Routine data (Clinical charts, clinic HIV testing and tracking registers, patient folders and TIER.Net*)
• Association between SDPs processes and linkage to and retention in care and psychosocial factors including social support and age-appropriate disclosure, health literacy and beliefs, HIV stigma and expectations of health services	• Proportion initiating ART immediately after a positive HIV test at SDPs	• Baseline and follow-up questionnaires

*TIER.Net is an electronic patient management system used to capture patient-level data on HIV management in South Africa. **NHLS:** National health laboratory system; **RMS:** Rapid Mortality Surveillance; **AGYW:** Adolescent girls and young women; **ABYM:** Adolescent boys and young men; **ART:** Antiretroviral therapy; **SDPs:** Service delivery points.

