At least one enrolled participant from each participating SDPParticipants who tested HIV-positive at participating SDPs who did and did not link to care within 14 days, and who did and did not remain in care at 6 months after their diagnosis, if non-linked participants can be reachedParticipants who enrolled in the study and responded to the baseline interview but did not test for HIV.

Furthermore, KIIs will be conducted with 22 purposively selected stakeholders including reproductive and healthcare providers at different sites and primary health care centers. The KIIs will focus on the barriers to, and facilitators of linkage to care, and perspectives of ways to improve the uptake of HIV treatment and care services to describe the relative success of different HIV treatment service delivery models. During the KIIs, process mapping will also be conducted to understand the processes and steps involved in the delivery of the services in each of the models. In this case, emphasis will be placed on the inputs, outputs, and outcomes. The duration of the IDIs, and KIIs will range from 60–120 minutes depending on how the discursive and interactive process unfolds.

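### The primary linkage outcome is defined twice with different windows for the CD4 route: 14 days in the Study design text, 1 month in Table 4

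*Protocol article*

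**What the plan says.** The Study design section of the protocol article opens its outcome paragraph with "The primary outcomes for this study are linkage to care within 14 days and retention in care at six months after HIV diagnosis". The formal definition that follows gives two ways to count as linked: ART initiation evidenced by a TIER.Net record, or being someone "for whom baseline CD4 results have been captured into their TIER.Net record within 0–14 days (within 2 weeks) of their HIV-positive test".

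Table 4, under Data collection, lists the outcome variables. Its first row is labelled as a primary outcome and also has two routes. The ART route covers those "who have initiated ART as evidenced by a record in their TIER.Net within 14 days". The CD4 route covers those "for whom baseline CD4 results have been entered into their TIER.Net record within 1 month of their HIV-positive test result".

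The 14-day window appears once more, in the in-depth interview sampling, which seeks participants "who did and did not link to care within 14 days". The Sampling section says that linked and unlinked interviewees are identified from the 1-month follow-up data. That fixes when status is looked up, not which window defines it.

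**The concern.** Both passages are current text and both claim to define the primary outcome. They agree on 14 days for ART, if the outcome statement is read as applying to both routes. They disagree on the CD4 route, and no rule of precedence is given. Two analysts could each follow the article faithfully and report different primary proportions, and the choice between them could be made after the data are seen. Quantifying linkage across service delivery models is a stated objective, so the ambiguity reaches the main comparison.

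A second, smaller issue is shared by both versions. The CD4 route stops the clock when the result is captured or entered in TIER.Net. A result that exists but is typed in late can therefore turn a linked participant into an unlinked one, and the shorter the window, the more this can happen.

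**Working it through.** **1. The two definitions side by side** (1 month taken as 30 days; 14 days taken to apply to ART in both)

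| Participant | Study design text | Table 4 |
|---|---|---|
| ART by day 14 | linked | linked |
| No ART by day 14, CD4 entered by day 14 | linked | linked |
| No ART by day 14, CD4 entered on days 15–30 | **not linked** | **linked** |
| No ART by day 14, CD4 entered after day 30 or never | not linked | not linked |

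Only the third row differs. Everyone linked under the text is linked under Table 4, so with x the share of participants in the third row:

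p(Table 4) = p(text) + x, with x ≥ 0.

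**2. Planning figures, as background**

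The Sampling section gives "11 in each model with 50 participants per cluster assuming an intraclass correlation coefficient (ICC) of 0.01 and significance level of 0.05". Table 2 gives 62% vs 72% and power 0.89.

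- Participants per model: 11 × 50 = 550, so 1 percentage point is 5.5 participants.
- Design effect: 1 + (50 − 1) × 0.01 = 1.49.
- Effective n per model: 550 / 1.49 = 369.1.
- Power = Φ{[d − z·√(2p̄(1−p̄)/n)] / √[(p1(1−p1) + p2(1−p2))/n]}, where d is the difference and p̄ the mean of the two proportions.
- For 0.62 vs 0.72: d = 0.10; √(2 × 0.67 × 0.33 / 369.1) = 0.0346; √((0.2356 + 0.2016) / 369.1) = 0.0344.
- One-sided 0.05 (z = 1.645): (0.10 − 0.0569) / 0.0344 = 1.25, power 0.895, which matches the stated 0.89.
- Two-sided 0.05 (z = 1.96): (0.10 − 0.0678) / 0.0344 = 0.93, power 0.825.

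The article does not state the sidedness. The point here concerns the outcome definition, not this figure. The two-sided value is the reference below.

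**3. What x could do**

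The documents do not give x, overall or by model. Assumed range: 0 to 10 points per model, added to 62% (lower model) and 72% (higher model) as if those were the 14-day proportions.

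| Added to lower | Added to higher | Table 4 proportions | Difference | Two-sided power |
|---|---|---|---|---|
| 0 | 0 | 62% vs 72% | 10 points | 0.825 |
| 5 | 5 | 67% vs 77% | 10 points | 0.858 |
| 10 | 10 | 72% vs 82% | 10 points | 0.899 |
| 5 | 0 | 67% vs 72% | 5 points | 0.314 |
| 10 | 0 | 72% vs 72% | 0 points | – |
| 0 | 5 | 62% vs 77% | 15 points | 0.994 |

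Equal shares move the level and leave the difference at 10 points. Unequal shares move the difference by the gap between them. Five points in one model is 0.05 × 550 = 27.5 participants.

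**The case against.** The strongest reply is that the article is not evenly split. The outcome statement, the formal definition and the interview sampling all use 14 days; Table 4 is introduced as an overview and stands alone. The study is also non-randomised and described as exploratory. The affected group is narrow, since anyone starting ART within 14 days is linked under both versions, and the abstract reports that same-day initiation has increased. The planned Cox analysis of time from positive test to ART initiation does not use the CD4 window at all.

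All of this stands, and it shows which way to reconcile. It does not remove the conflict, because the Table 4 row carries the primary-outcome label and nothing ranks it below the text.

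A reader might also infer more than the documents support:

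- **That the whole outcome is timed by data capture.** This is clear only for the CD4 route. For ART, the TIER.Net record is the evidence of initiation, and the wording leaves open whether the 14 days run to the initiation or to the record. Table 4 lists the ART initiation date among its variables.
- **That Table 4 sets 1 month as the benchmark for entering baseline CD4 results.** The line in question, "TIER.Net records at facility of NHLS results recorded within 1 month of the date each sample was sent", is an example variable under six-month retention. It says nothing about baseline CD4.
- **That capture delay differs between models and so biases the comparison.** No section says so. Table 3's footnote connects primary health care facilities to all 22 service delivery points but does not mention delay.

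**Conclusion.** The contradiction is real and needs correcting: as written, the primary linkage result depends on which passage is followed. The direction is certain, given a 14-day ART window in both versions: Table 4 yields an equal or higher proportion. The size is unknown, because the share with no ART by day 14 and a CD4 result entered on days 15–30 is not in the documents; it could be close to zero.

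An effect on the model comparison is conditional on that share differing by model. A 5-point excess in the lower model would halve the planned difference, and a 10-point excess would remove it. These are illustrations over an assumed range, not estimates. That the CD4 route partly measures data-entry delay is likewise a possibility created by the wording, not something the documents demonstrate.

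**What to change.** 1. Put one definition of linkage in both the Study design section and Table 4, with the 14-day window for both routes, as in the outcome statement and the interview sampling.
2. State for the ART route and for the CD4 route whether the event date or the TIER.Net capture date decides if the window is met.
3. Name the version with 1 month for CD4 as a sensitivity analysis, and report by model the number of participants who change status between the two versions. This shows directly whether the choice matters.
4. Settle this before linkage outcomes are examined by model. If they have already been examined, say so and report both versions.

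Dating the CD4 route by specimen collection is optional and has a drawback. The documents do not say when the baseline sample is taken; if it is drawn at the testing visit, everyone sampled would count as linked on day 0.

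The cost is a wording change in two places and at most one extra date field, from TIER.Net and laboratory sources the study already uses.
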